### Measurements

**Table 1** shows the variables measured in the WAHA trial and how often they were measured.

**Table 1 T1:** Measurements in the Walnuts and Healthy Aging (WAHA) study.

Measurements	Content	Baseline	Year 1	Year 2
Eligibility questionnaire	Sex, age, inclusion, and exclusion criteria	X		
General/quality of life questionnaire^∗^	Marital and socioeconomic status, medical conditions, medication	X		X
Follow-up questionnaire, including withdrawal	Symptoms and conditions, tolerance, medication changes		X	X
Food frequency questionnaire (FFQ)^†^	Multiple food groups and foods	X		X
Diet recalls^‡^	All daily foods and beverages	X	X	X
Physical activity questionnaire	Short-version of the Minnesota questionnaire	X	X	X
Clinical blood pressure		X	X	X
Electrocardiogram^¶^		X		X
Anthropometric measurements	Height, body weight, waist, and hip circumferences, % body fat^§^	X	X	X
Neuropsychological evaluation	A complete test battery to assess cognitive function	X		X
Ophthalmological examination	Optic nerve and macular optical coherence tomography	X		X
Standard blood chemistry	Lipid profile, glucose, insulin, renal function, liver function, blood count, others	X	X	X
Serum inflammatory and oxidative stress markers	CRP, E-selectin, others	X		X
Urine chemistry	Albumin, total polyphenols, ellagitannin, urolithins, others	X	X	X
Red blood cell fatty acids	Measure of compliance, performed in 30% of the cohort	X	X	X
Genomic studies	*APOE*, others	X		
Brain MRI^¶^	Performed in a subset (*n* = 120)	X		X
B-mode ultrasonography of carotid arteries^¶^	Carotid intima-media thickness and plaque burden	X		X
DEXA^§^	Body composition and bone mineral density	X		X
Twenty-four-hour ambulatory blood pressure monitoring^¶^	Performed in 80% of the cohort	X		X
Leukocyte telomere length^¶^	Performed in all participants at baseline and only in those with brain MRI at 1 and 2 years	X	X	X
Serum miRNAs^¶^	miRNAs involved in lipoprotein metabolism	X	X	

*BCN, Barcelona; LLU, Loma Linda University; CRP, C-reactive protein; MRI, magnetic resonance imaging; DEXA, dual-energy X-ray absorptiometry; miRNAs, microRNAs.*

*^∗^The general questionnaire was collected at baseline at both sites. At LLU this questionnaire was called the Quality of Life questionnaire and was collected at end of year 2 also and included more questions about the subjects’ mental health and well-being.*

*^†^Forty-four-food groups and items FFQ at baseline and year 2 at BCN; 150-food group and items FFQ once during the 2nd year at LLU.*

*^‡^Three-day (including one weekend day) self-recorded recalls in BCN at baseline, years 1 and 2; five unannounced 24-h recalls by telephone at LLU over 2 years.*

*^§^ Percent body fat measured by bioelectric impedance at LLU and by DEXA in BCN.*

*^¶^ Determined only at the BCN center.*

#### Measurements at Both Sites

##### Dietary assessment

In BCN, a food frequency questionnaire (FFQ) including 44 food groups was administered to all participants at baseline and end of year 2. In LLU, after the 1st study year, participants filled in a FFQ validated in a pilot sample of elderly persons (Segovia-Siapco et al., 2007). During the study, dietary intake was monitored by conducting five unannounced 24-h diet recalls over 2 years (LLU) or 3-day food records every 6 months (BCN). Participants allocated to the walnut diet who had difficulty chewing due to dental problems were given a coffee grinder at no cost, with instructions on how to consume the ground walnuts by incorporating them to semifluid foods such as yogurt.

##### Clinical evaluation

A clinician saw the participants at baseline, when a general questionnaire was filled in, and at the end of the study, when a follow-up questionnaire was administered to assess final changes in clinical status and medication and adverse events. In the same visit clinical blood pressure was measured following the recommendations of the European Societies of Hypertension and Cardiology (ESH/ESC) (Mancia et al., 2013): after a 5-min rest with the patient seated in a quiet environment, three measures of BP were taken at 2-min intervals with a validated semiautomatic oscillometer (Omron 705-CP, Omron Healthcare Group, Kyoto, Japan). The mean of the last two measurements of systolic and diastolic blood pressure was recorded as office blood pressure. An electrocardiogram (ECG) was performed at baseline and end of study.

##### Physical activity, anthropometry, and body composition

Physical activity was evaluated at baseline, year 1, and the end of the study with a validated short version of the Minnesota questionnaire (Elosua et al., 1994). The dietitians measured height at baseline and 2 years using a wall mounted stadiometer, body weight at baseline and every 2 months by calibrated scales, and waist and hip circumferences every 6 months by using an anthropometric tape midway between the lowest rib and at the iliac crest and at the widest point in the hips, respectively. Body composition was assessed at baseline and 2 years by bioelectric impedance using a body composition analyzer (Tanita, Model TBF-300A, Arlington Heights, IL, USA) at LLU and by dual energy X-ray absorptiometry (DEXA) (Whole body scanner GE-Lunar IDXA, GE Healthcare, Madison, WI, USA) at BCN.

##### Cognitive testing

A comprehensive neuropsychological test battery evaluating several cognitive domains was administered at baseline and at the end of the trial. Neuropsychologists who were masked to participant’s group assignment conducted the cognitive tests. The instruments used were Block design from the Wechsler Adult Intelligence Scale (WAIS III) (Wechsler, 1997), Rey-Osterrieth Complex Figure (ROCF) (Rey, 1941), Rey Auditory Verbal Learning Test (RAVLT) (Rey, 1958), Boston Naming Test (Kaplan et al., 2001), Semantic category evocation of animals (Ramier and Hécaen, 1970), Number location and incomplete letters from the Visual Object and Space Perception Battery (VOSP) (Warrington and James, 1991), Trail Making Test, parts A and B (Partington and Leiter, 1949), Phonemic fluency (FAS) (Benton and Hamsher, 1976), Stroop Color Word Test (Stroop, 1935), Symbol Digit Modalities Test (SDMT) (Smith, 1973), Digit span forward and backward from the WAIS III (Wechsler, 1997), and the Conners Continuous Performance Test (CPT II) (Conners and Staff, 2000).

Subjects’ raw test punctuations were standardized to *z* scores to generate a global cognition composite by computing the mean standardized changes of all neuropsychological tests. This composite was pre-specified as the primary outcome of the study. Moreover, composites of cognitive domains analyzed separately were calculated. First, the memory composite included the mean standardized individual change scores of the RAVLT (immediate and delayed recall) and the 3-min recall of ROCF. Language composite included scores from animal semantic fluency and the Boston Naming Test. Perception composite included scores from number location and incomplete letters from VOSP battery and block design from WAIS-III battery. Finally, a composite score related to frontal functions was created including scores from TMT parts A and B, FAS, Stroop, SDMT, digit span from WAIS-III, and CPT-II. As secondary outcomes, composites assessing cognitive domains separately were defined.

In addition, information about cognitive reserve and mood was collected using a cognitive reserve questionnaire (Solé-Padullés et al., 2009) and the Hamilton Depression Rating Scale (Hamilton, 1967), respectively. Premorbid intelligence was assessed with the American National Adult Reading Test (Grober and Sliwinski, 1991) at LLU site and the Word Accentuation Test (Del Ser et al., 1997) at BCN site.

##### Ophthalmologic evaluation

Retinal examinations were performed at baseline and end of the study by ophthalmologists (BCN) and trained technicians under the supervision of an ophthalmologist (LLU). The central and average thickness and volume of the macular neurosensorial retina and the thickness of the retinal nerve fiber layer were ascertained by OCT (Cirrus HD OCT, Zeiss, Germany).

##### Biochemical measurements

Fasting blood samples and morning spot urine samples were collected at baseline and end of years 1 and 2, and aliquots of EDTA plasma, serum, buffy coat for DNA recovery, whole blood, and urine samples are kept frozen at -80°C. Participants reported on the assigned days after fasting for a minimum of 12 h. An experienced phlebotomist drew blood and samples were centrifuged and aliquoted for the various assays and stored immediately at -80°C. All assays except routine chemistry for safety assessment and determination of the *APOE* genotype were performed at the end of the study to control for between-assay variability. Extra aliquots were stored for additional outcomes of interest to the investigators that might arise during or after the completion of the study. Samples were shipped overnight on dry ice to the appropriate laboratories for biochemical determinations once the study was completed. Plasma and/or serum samples will be used to determine changes in lipid profile, glycemic control, liver and renal function tests, and inflammation and oxidation biomarkers. Extra aliquots of all samples have been stored at -80°C. To reduce assay variability, all samples for a specific assay will be run together in the same laboratory.

An objective biological marker of compliance with walnut consumption, the RBC fatty acid proportions of ALA (Sala-Vila et al., 2011), was assessed in a randomly selected subset (30% of participants) at baseline and years 1 and 2. Given that walnuts have one of the highest polyphenol content of all edible plants (Carey et al., 2013), the urinary content of total polyphenols (Valls-Pedret et al., 2012) will also be used as an indirect marker of compliance.

##### Genetic testing

The *APOE* genotype will be determined by using the method of Hixson and Vernier (Hixson and Vernier, 1990).

#### Measurements Only at BCN Site

Some techniques were performed only at the BCN center based on prior expertise, availability, and cost.

##### Brain magnetic resonance imaging

Approximately 120 participants underwent brain MRI at baseline and 2 years using a 3-tesla scanner (Magnetom Trio Tim, Siemens, Germany). The protocol included high-resolution 3D structural datasets, a diffusion tensor imaging sequence, a Pulsed Arterial Spin Labeling (PASL)-MRI perfusion sequence, a fluid attenuated inversion recovery (FLAIR) image sequence, and a functional sequence with an n-back working memory task.

##### Carotid ultrasonography

Bilateral carotid artery ultrasound imaging was performed at baseline and 2 years according to a standardized protocol (Sala-Vila et al., 2014). Main outcome measurements were mean and maximum carotid IMT and plaque presence, maximum height and area. Briefly, patients underwent sonographic assessment with an Acuson X300 ultrasound system (Siemens, Germany) equipped with a VF 10-5 linear multifrequency transducer (frequency range 5–10 MHz) and ECG synchronization. The same certified sonographer performed all examinations without knowledge of group allocation. Secondary outcomes were mean and maximum IMT at each carotid segment. IMT was defined as the average of multiple distance readings between the far wall lumen–intima and media-adventicia interfaces taken bilaterally at common carotid artery 1 cm pre-bifurcation, bifurcation, and internal carotid artery 1 cm after the flow divider. Plaques were sought by using B-mode and color Doppler examinations in both longitudinal and transverse planes to take into consideration circumferential asymmetry and were defined as a focal wall thickening encroaching into the arterial lumen by at least 50% of the surrounding IMT value or with thickness of at least 1.5 mm as measured from the media adventitia interference to the intima-lumen surface. IMT and plaque measurements were taken oﬄine by using edge-finding software in the predefined segments of the arterial wall. Plaque height was recorded at the more appropriate view, either longitudinal or transversal. Plaque area was determined by the technique of Spence et al. (2002). Plaque burden was recorded for all study subjects and defined in two ways: the sum of maximum heights of all plaques and the sum of areas of all plaques.

The same certified sonographer blinded to treatment allocation performed all scan readings. Consistency (reliability or repeatability) of ultrasound carotid wall measurements was evaluated by comparing results from repeated examinations in 14 subjects performed 3 days apart. Intraclass correlation coefficient ranged from 0.92 to 0.96 for IMT mean (average of right and left) and IMT maximum (maximum value from either right or left) in common, bulb, and internal carotid segments.

##### DEXA studies

Total body lean and fat mass distribution and bone mineral density were assessed by DEXA at baseline and 2 years. This is a standard procedure performed using the whole-body scanner GE Lunar iDXA (GE Healthcare, Madison, WI, USA) according to the manufacturer’s specifications. The iDXA is a narrow fan-beam DXA instrument with a high weight limit (204 kg) and a relatively wide scanning space (66 cm) designed to accommodate obese subjects. The subjects were positioned in the center of the table for each scan. The appropriateness of patient’s position was further assessed by the DXA software by means of an automatic detection system. The instrument has three scan modes that adjust the X-ray attenuation for the thickness of each patient. For this study, scans were performed using the default scan mode automatically selected by the DXA software. The GE Lunar Body Composition Software was used to obtain fat-free mass (FFM) and fat mass (FM) measurements, as well as segmental FM and FFM distribution (trunk, right and left upper limb, right and left lower limb, android, and gynoid) (Hull et al., 2009).

##### Ambulatory blood pressure monitoring

Twenty-four-hour ambulatory blood pressure was monitored in 67% of participants selected at random at baseline and 2 years, following the ESH/ESC recommendations (Mancia et al., 2013; Doménech et al., 2014). The devices were Spacelabs 90207/90217 (Spacelabs^®^ Inc., Richmond, WA, USA), programmed for blood pressure lectures every 20 min during the day and every 30 min at night. Each participant kept a diary of daily activities and times of going to bed and waking up. The report included the duration of monitoring (h), the proportion of valid blood pressure registers, and the mean values of systolic and diastolic blood pressure during periods of activity, rest and the total recording period.

##### Telomere length

Leukocyte telomere length was determined in all participants at baseline and in those undergoing sequential brain MRI at the end of years 1 and 2. Fresh peripheral blood mononuclear cells were separated from 5 mL of EDTA-collected blood by Ficoll gradient centrifugation and also stored at -80°C until determination of telomere length by HTQFISH, which involves *in situ* hybridization of telomere repeats to fluorescent primer and analysis by fluorescence quantification of confocal images.

##### MicroRNA

Finally, at baseline and 1 year circulating miRNAs potentially involved in lipoprotein metabolism will be screened by qRT-PCR in plasma samples. The procedure requires a sample of ∼1 mL plasma per measurement, kept in Trizol^®^ and stored at -80°C until the moment of the analysis.

### Statistical Analyses

Sample size calculation was based on prior results from the PREDIMED study (Valls-Pedret et al., 2015). We used as reference the 2-year unadjusted changes in RAVLT (total learning) scores in the Mediterranean diet enriched with nuts compared to the control diet. In order to have a 90% power to detect differences in the contrast with the null hypothesis, assuming mean changes of 1.05 and 2.10 points in the control and intervention groups, respectively, with a standard deviation of 4.00, the total number of participants required was 308 per group. Considering an estimated dropout rate of 10%, we needed to include a total of 686 participants.

All data collected in the study were entered into an online database (Onto CRF, Costaisa, Spain) managed for both centers. An oversight committee blinded to subject allocation monitored safety, quality of data collected, and trial’s progress.

Between-group differences in baseline neuropsychological and ophthalmologic data will be examined by ANOVA and further by ANCOVA adjusting for center, sex, age, education years, *APOE4* genotype, smoking, BMI, energy intake, physical activity, diabetes, hyperlipidemia, and hypertension. Changes for each individual cognitive test, cognitive composites, ophthalmologic evaluations, and foods and nutrients ensuing intervention will be assessed by ANOVA and further by ANCOVA adjusting for the variables listed above. Statistical significance will be set at the *P* < 0.05 level. Analyses will be performed using SPSS software, version 16.0 (IBM Corp., New York, NY, USA).

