### Outcomes

Primary outcomes are changes from baseline in the composite score of all neuropsychological tests for cognition and in the average thickness of the retinal nerve fiber layer of each eye, as assessed by optical coherence tomography (OCT). As secondary cognitive outcomes, we will analyze composites for different cognitive domains, including memory, language, perception, and frontal functions (for further detail, please see section Cognitive Testing); assess the incidence of AD according to NINCDS-ADRDA criteria (McKhann et al., 1984); and evaluate the incidence of MCI, defined by Petersen’s diagnostic criteria (Petersen et al., 2001). Secondary OCT outcomes are macula cube thickness, cube volume, and central thickness.

Other secondary outcomes for the whole cohort are changes in anthropometric measures, lipid profile, serum inflammatory and oxidative stress markers, red blood cell (RBC) fatty acids, and urinary polyphenols. At the BCN site, the following secondary outcomes will be assessed: structural and functional brain MRI variables, carotid intima-media thickness (IMT) and plaque burden, body composition, bone mineral density, 24-h ambulatory blood pressure, leukocyte telomere length, and serum miRNAs.

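### The covariate list for the change-score ANCOVA omits the baseline value of the outcome, which forgoes precision and leaves part of any chance baseline difference in the estimate

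*Protocol article*

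**What the plan says.** Under Outcomes, the cognitive primary is a change: "Primary outcomes are changes from baseline in the composite score of all neuropsychological tests for cognition". The second primary is the change in average retinal nerve fiber layer thickness of each eye. Under Cognitive testing, raw test scores are standardized to "generate a global cognition composite by computing the mean standardized changes of all neuropsychological tests".

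Statistical Analyses first deals with the comparison of the arms at baseline: "Between-group differences in baseline neuropsychological and ophthalmologic data will be examined by ANOVA", followed by "ANCOVA adjusting for center, sex, age, education years", then APOE4 genotype, then "smoking, BMI, energy intake, physical activity, diabetes, hyperlipidemia, and hypertension". That makes 4 + 1 + 7 = 12 covariates. The next sentence turns to the effect of the intervention: "Changes for each individual cognitive test, cognitive composites, ophthalmologic evaluations, and foods and nutrients ensuing intervention will be assessed by ANOVA and further by ANCOVA". The adjustment set is carried over by reference: "further by ANCOVA adjusting for the variables listed above".

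Table 1 schedules the neuropsychological evaluation ("A complete test battery to assess cognitive function") and the ophthalmological examination at baseline and year 2. Participants and Eligibility Criteria and Stepwise Procedures both place these baseline tests before randomization.

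**The concern.** The list was drawn up for an analysis in which the baseline outcome is the dependent variable and so cannot be a covariate. Applied unchanged to changes, it leaves out a covariate that is measured before randomization, belongs to the outcome itself and is already collected. No other section adds it.

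A change score contains its own baseline. When baseline and follow-up have similar variances and correlate below 1, change is negatively correlated with baseline (regression to the mean). Two things follow if baseline is left out. Variance that the baseline could explain stays in the error term. And if the arms differ at baseline by chance, part of that difference appears in the estimated effect. Adjusting for age, education, center and the rest removes some of this, but only so far as those variables predict the baseline score.

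Because the article states its adjustment set as a fixed list, this is a feature of the stated plan rather than a detail left to a fuller document.

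**Working it through.** **Inputs from Statistical Analyses.** Mean RAVLT changes 1.05 (control) and 2.10 (walnut), so the difference is 1.05. SD 4.00, read as the SD of the change. Power 90%. Significance level 0.05; sidedness is not stated and two-sided is assumed. 308 per group; 10% dropout; 686 in total. The reference is the unadjusted change.

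**Assumed.** The correlation rho between baseline and year 2 is not in the article; the range 0.5 to 0.9 is used. Baseline and follow-up variances are taken as equal and allocation as 1:1.

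**Step 1: reproduce the sizing.** n per group = 2(1.960 + 1.282)² × 4.00² / 1.05² = 305 (306 with the exact t distribution), against 308 stated. A one-sided test would give 249, which does not fit, so two-sided is implied. Dropout: 308 / 0.9 = 342.2, rounded up to 343; 2 × 343 = 686, as stated. Power at 308 per group is 90.3%.

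**Step 2: effect of baseline adjustment on variance.** With outcome SD s at each time:

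- variance of the change = 2(1 - rho)s²
- residual variance after baseline adjustment = (1 - rho²)s²
- ratio = (1 + rho)/2, so the residual SD is 4.00 × √((1 + rho)/2)

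**Step 3: effect of a chance imbalance.** If the walnut arm starts D above control, the change-score estimate shifts by -(1 - rho)D. The outcome SD implied by a change SD of 4.00 is s = 4.00 / √(2(1 - rho)). For D = 0.1 SD the size of the shift is (1 - rho) × 0.1 × s.

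| Assumed rho | Variance ratio | Residual SD | n per group for 90% power | Power at 308 per group | Implied s | Shift for 0.1 SD imbalance |
|---|---|---|---|---|---|---|
| no baseline term | 1.00 | 4.00 | 305 | 90.3% | – | – |
| 0.5 | 0.75 | 3.46 | 229 | 96.4% | 4.00 | 0.20 |
| 0.7 | 0.85 | 3.69 | 260 | 94.2% | 5.16 | 0.16 |
| 0.9 | 0.95 | 3.90 | 290 | 91.6% | 8.94 | 0.09 |

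Against the 1.05-point target, these shifts are about 19%, 15% and 9%.

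**Step 4: how likely is a 0.1 SD imbalance?** Completers are 362 - 38 = 324 and 346 - 34 = 312 (Table 2 and Anticipated Results). The standard error of D is √(1/324 + 1/312) = 0.079 SD. A difference of 0.1 SD or more in either direction is 0.1 / 0.079 = 1.26 standard errors, which arises by chance in about one trial in five.

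**The case against.** Several points on the other side stand.

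- **Size.** The calculation compares baseline adjustment with a plain change score. The planned ANCOVA already holds 12 covariates, some of which may predict the baseline score, so the gain over it depends on partial correlations that the article does not give.
- **Outcome.** The figures are for RAVLT total learning. The cognitive primary is a mean of standardized changes, and if each change is scaled by its own SD, the (1 + rho)/2 ratio does not carry over directly. Nothing in the article allows a calculation for the retinal outcome. A composite of many tests may well have a high rho, where the gain is small.

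A reader might also infer stronger faults, which the document does not support.

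- **That the primary estimate is biased.** Under randomization the change-score estimate is unbiased on average and its test is valid. The shift is conditional on the imbalance that happens to occur, and only the fraction (1 - rho) of it enters.
- **That the trial is underpowered.** Sizing rests on the unadjusted change and reproduces. The 636 completers exceed the 2 × 308 = 616 required.
- **That the stratification factors are ignored.** The unadjusted ANOVA leaves them out, but the planned ANCOVA includes center, sex and age.
- **That two competing primary models are left open.** An unadjusted analysis followed by an adjusted one is ordinary, and which of them decides may be settled in an analysis plan that is not shown.

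None of this supplies the missing covariate. The list is closed and the baseline value is not on it.

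**Conclusion.** The point holds as a worthwhile improvement to the stated analysis, not as an error of validity or of sample size. The plan forgoes precision and leaves a fraction (1 - rho) of any chance baseline difference in the estimate. On the RAVLT illustration the variance reduction is 5% to 25%, and power at 308 per group would be about 92% to 96% instead of 90%, for rho from 0.9 down to 0.5. These figures rest on an assumed rho, equal variances at the two times, 1:1 allocation and a comparison with an unadjusted change score. The benefit over the 12-covariate ANCOVA, and for the composite and retinal outcomes, is unknown and may be smaller or larger.

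**What to change.** In Statistical Analyses, give the ANCOVA for changes its own covariate sentence instead of referring back to the baseline comparison, and add the baseline value of the outcome being analyzed:

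- for global cognition, a baseline composite z score built from the same tests as the change composite;
- for the retinal nerve fiber layer, the baseline thickness of the same eye or eyes.

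Keep center, sex, age and the other listed covariates. Take the primary estimate for each primary outcome from this baseline-adjusted ANCOVA and report the unadjusted ANOVA as supportive. The article describes these analyses in the future tense, so the change can be made before they are run.

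The cost is a sentence or two, plus a definition of the baseline composite, since the article defines the global composite only on changes. No new data are needed.
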